### Limitations of prior work

In a review of studies reporting increased long-term risk for LDs, Janki et al. identified that both the Norwegian study reporting an increased risk of CVD, mortality, and ESKD, and the US study reporting increased risk of ESKD, selected non-donor control populations that were healthier than the donors, resulting in an over estimation of risk [103]. In addition, the definition of ESKD differed between donors and non-donors in the US study, potentially biasing the results. A meta-analysis of the cardiac studies concluded that there was no increase in CVD disease or mortality in LDs [104]. For the two studies identifying an increased risk of ESKD among LDs, the number of events was small, and there have been additional concerns about methodology, including: controls were non-contemporaneous and from a different geographic location; lack of renal function assessment for controls at the date corresponding to the date of donation; and concerns about the choice of statistical methods [105–115].

A key limitation in existing studies is that there was no determination of family history of chronic kidney disease (CKD) or ESKD for controls. In the Norwegian study, all 9 donors who developed ESKD were first-degree relatives of the recipient; in the US study, 83 of the 99 who developed ESKD were related to the recipient. Numerous studies in the general population have shown that individuals related to a person with ESKD have an increased risk of ESKD [116–122]. Wainright et al., using the Organ Procurement and Transplantation Network (OPTN) database, reported that LDs who were first-degree relatives of the recipient had significantly increased risk of ESKD (highest in identical twins) compared to LDs who were distant relatives or were unrelated to the recipient [123].

There have only been a few studies of pregnancy risk postdonation [100–102, 124, 125]. Studies have been limited by low numbers of events, and the design has generally been restricted to a before-and-after study design which may result in an over estimation of risk.

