### Study cohorts

#### UMN LD cohort

From January 1, 1963 through December 31, 2012, there were 4022 LDs at UMN who met the study criteria. Most LDs were from the upper Midwest region of the US, and detailed descriptions of the UMN LD cohort have been published [45, 50]. At donation, laboratory and demographic variables, surgical information, and peri-operative course information is collected. Prior to 2003, LDs were surveyed intermittently. In 2003, all donors were contacted to be surveyed and asked to consent to be surveyed every three years. Since 2003, consenting LDs are surveyed postdonation at regular intervals (6, 12, and 24 months, and then every 3 years). Those not returning to the clinic are sent a survey (by mail; or, if preferred, by email) to determine health status. If the survey is not returned, the LD is contacted by phone monthly, for 3 months. At least one phone call is made in the evening and one on weekends to increase response rates. LDs are also asked to provide alternate contacts. For LDs who become lost to follow-up UMN uses these contacts to ask for a current phone number and address. Available internet search engines and other databases (e.g., Accurint.com, Peoplefinder.com) are also used to identify LDs lost to follow-up.

At each contact, LDs are asked about hypertension, DM, and other diagnoses requiring treatment. Female donors are asked about pregnancy history. LDs are also asked to provide recent lab test results and copies of medical records; alternatively, with LDs’ permission, UMN investigators contact local clinics for recent medical records that include clinical notes and laboratory test results, including serum creatinine, glucose, urinalysis, and urinary protein measurements. Those without recent information are asked to get a history, physical, and labs at their local physician’s office and have the results sent to UMN. For LDs willing to do the tests but without insurance coverage, UMN pays for them. A summary of the clinical and demographic characteristics of the UMN LD cohort is given in Table 1.

**Table 1 Tab1:** Characteristics of the University of Minnesota (UMN) and Mayo Clinic donors

	UMN donors (N = 4022)	Mayo donors (N = 3035)
Years from donation to last survey or History & Physical (mean ± SD)	22.04 ± 11.93	
No returned surveys	9.5%	
Sex (%)		
Female	2294 (57.0%)	1668 (55.0%)
Male	1728 (43.0%)	1354 (44.6%)
Unknown	0 (0%)	13 (0.4%)
Age at donation (mean ± SD)	39.02 ± 11.64	42.52 ± 11.98

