Similar to the donor candidate assessment, certain conditions are allowed for controls at the time of index if they are otherwise healthy. A BMI of 35–40 kg/m^2^ is allowed if the control is deemed to be in otherwise very good health as BMIs in this range are allowed in some donors. As with donors, medically well-controlled hypertension is allowed in controls over 50 years of age. Controls on more than 1 non-diuretic antihypertensive medication or more than 1 diuretic antihypertensive medication are excluded. Depression/anxiety is allowed if well controlled, infrequent, and acute episodes had occurred in the distant past relative to the index date. Substance abuse is also allowed if use was in the remote past; current marijuana and alcohol use is allowed as long as it does not interfere with work and social function. Patients who were pregnant at the index date or within 3 months postpartum, or hospitalized within 2 weeks of index date (for a non-exclusionary reason), may be rematched to a different donor at a different index date.

If it is unclear if a certain control would have been eligible to donate given their medical history, a review by kidney donation experts (Drs. [name], [name], and [name]) is used to approve or exclude the potential control. The abstraction guidelines are subsequently updated to ensure future consistency. In addition, the abstractor team meets monthly after completing a reliability chart (same chart for each abstractor) to ensure similar abstractions among the abstractor team.

If a control is validated, abstractors proceed to collect additional baseline and follow-up data. This includes any mention of family history of DM, hypertension, CKD, or ESKD. We obtain the closest laboratory data measures before and after the index date for baseline. These measures include: height, weight, blood pressure (avoiding blood pressure obtained during visits to the emergency department), serum creatinine, blood urea nitrogen (BUN), serum glucose, urine glucose, and any assessment of proteinuria/albuminuria (avoiding those with concurrent urinary tract infections).

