We plan to use optimal, sparse 1:k matching with refined covariate balance[148, 149] to ensure that the patients who are in each group (donors and controls) are as similar as possible based on age, sex, race/ethnicity, BMI, systolic and diastolic blood pressure, hypertension, smoking history, and family history of CKD. Briefly, this method allows one to exactly match on a small number of covariates (in this sense the method is sparse because it does not consider all possible matched pairs). The matching algorithm allows the near fine balance on discrete covariates between the intervention and control group (this means the distribution of the covariate is the same in the two groups but individuals may be matched to others with different levels of the covariate, i.e., frequency matching). An advantage of this approach is that it allows prioritization for balance on certain covariates over others. Finally, individuals are matched to minimize the overall difference between individuals using Mahalanobis distance or difference in propensity score (in this sense the match is optimal). The number of matched controls will depend on the number of potential controls with the available data. For each cohort of matched controls, we will assess the quality of matches by 1) computing the standardized difference of means for each covariate, as well as two-way interactions and squares and 2) for continuous covariates, examining quantile–quantile (QQ) plots, which compare the empirical distributions of each variable in the donor and control groups. Covariates for which there is an imbalance (e.g., standardized mean difference greater than 0.1) may be discretized and matched either exactly or to achieve near fine balance. Because matching is part of the design phase (as opposed to the analysis phase), we can repeat the matching several times until an acceptable balance is achieved without inflating type I error rates. If not enough controls with a matching characteristic (e.g., family history of CKD) are identified for matching to LDs, then the presence of the characteristics in both LDs and controls will be corrected for with multivariable adjustment for the analyses in predicting outcomes. Given that causal analysis is a rapidly developing field we will additionally consider state-of-the-art methodologies for determining optimal matches as new discoveries are made in this field.

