We will also evaluate if the effect of donation differs across baseline characteristics (i.e. evaluate if a characteristic modifies the effect of donation) by testing the significance of the interaction term between donation and the characteristic in the model. These models will also allow us to assess the attributable risk of donation in LDs with certain characteristics at donation. We will specifically assess if age, BMI, smoking, donation eGFR, and race/ethnicity modify the effect of donation on ESKD and mortality. As a sensitivity analysis, the analyses will be repeated using a subset of REP controls having at least 5 years of medical history preceding the index date.

Logistic regression models fit using generalized estimating equations will be used to test for differences in the odds of gestational hypertension and preeclampsia between LDs and controls for all pregnancies occurring after the index date, while accounting for women having potentially multiple pregnancies. Adjustment variables to be considered in the model include: race/ethnicity, age at pregnancy, gravidity, and previous occurrence of pregnancy complications. Secondary analyses using logistic regression models will test for differences in the odds of these complications in the first pregnancy after the index date, adjusting for having previous pregnancies, and second pregnancy after the index date, adjusting for the occurrence of pregnancy complications in the first post-index date pregnancy.

A linear mixed effects model will be used to test the difference in the trajectory of eGFR over time between living LDs and healthy controls. This model will initially have a linear effect for time with subject-specific random intercepts and slopes, but natural splines will be used to investigate nonlinear temporal trajectories.

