#### Power

Given the results identified using preliminary matching algorithms and chart review we assume that we will be able to identify 3 controls for 98% of LDs and at least one of those controls will be included in a more restrictive matched subset (i.e., known presence of CKD, known serum creatinine/urine protein at or prior to index date). For the following power analyses, the type-1 error probability is set to 5%.

For estimating the minimal detectible hazard ratio for all-cause mortality, we note that at present, 12% of UMN LDs, 7% of all Mayo LDs, and 11% of identified preliminary controls are deceased. With a mortality rate of 11% in our study population, we estimate that our minimal detectible hazard ratio with 80% power will be 1.13 for a 3:1 matching and 1.16 for a 1:1 matching.

In UMN LDs, approximately 13.5% have developed eGFR < 45 ml/min/1.73m^2^ during follow-up. In our analysis comparing the risk of developing an eGFR < 45 between UMN LDs and healthy controls, we conservatively estimate that eGFR < 45 will develop in approximately 8 to 14% of our study population. With this assumption, our minimal detectable hazard ratio will be between 1.20 and 1.15 for a 3:1 matching and between 1.25 and 1.18 for a 1:1 matching.

Among the 301 UMN LDs who developed DM after donation without first developing CVD, 57 individuals (19%) later developed CVD. Assuming identification of a 1:1 match for approximately 80% (240) of these donors and that the overall proportion of individuals in our study population who develop CVD after DM ranges from 15 to 23%, we will have 80% power to detect a hazard ratio between 1.94 and 1.70.

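### Family history of CKD is balanced as one ungraded factor although 69% of donors are first-degree relatives of a person with ESKD, and no listed analysis separates donors by relationship to the recipient

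*Protocol article*

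**What the plan says.** Under *Limitations of prior work*, the article calls the undetermined family history of controls a key limitation of earlier studies. It cites registry evidence that "LDs who were first-degree relatives of the recipient had significantly increased risk of ESKD (highest in identical twins", compared with donors who were distant relatives or unrelated.

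Under *Primary control group and matching algorithms*, the groups are to be made "as similar as possible based on age, sex, race/ethnicity, BMI, systolic and diastolic blood pressure, hypertension, smoking history, and family history of CKD". The same section says only that the investigators will try to bring family history of CKD into the match, from charts or the survey. If too few controls have a characteristic, its presence is handled by multivariable adjustment instead.

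For controls, *Control validation and medical record abstraction* describes the baseline data collected: "This includes any mention of family history of DM, hypertension, CKD, or ESKD".

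Under *Statistical analyses details*, the effect modifiers are named: "We will specifically assess if age, BMI, smoking, donation eGFR, and race/ethnicity modify the effect of donation on ESKD and mortality". Neither family history nor donor relationship is among them.

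Under *Control groups for sensitivity analysis*, groups i to iii drop family history and group iv imitates the matching of two earlier studies. All four vary the controls; none restricts the donors.

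**The concern.** Each of these first-degree donors has a close relative whose kidneys failed. A control who is positive because a chart mentions kidney disease in the family need not have a relative that close or that ill. If the matching variable does not separate these cases, the standardized differences and QQ plots will show balance on the coded variable while inherited risk still differs. The excess would then be reported as attributable to nephrectomy, chiefly for ESKD.

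This matters because removing familial confounding is a main reason given for the study. The hypothesis is of small differences, and the results are meant to feed a risk calculator for donor candidates. The planned negative control, non-kidney cancer, has no reason to react to kidney-specific inherited risk.

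**Working it through.** **1. Donor relationship (Table 1, UMN + Mayo).**
- Child 474 + 493 = 967; parent 932 + 422 = 1,354; full sibling 1,579 + 934 = 2,513; identical twin 15 + 5 = 20. First-degree total: 4,854/7,057 = 68.8% (UMN 3,000/4,022 = 74.6%; Mayo 1,854/3,035 = 61.1%).
- Half sibling 46 and other relative 397 bring all relatives to 5,297 (75.1%).
- Not related 1,224 + spouse 525 = 1,749 (24.8%; UMN 760, Mayo 989). Unknown: 11.

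**2. Possible residual bias for ESKD.** The article gives no kinship risk ratio, so every value here is an assumption. Let R1 be the ESKD risk ratio for a first-degree relative with ESKD (2 to 5), R2 the ratio for weaker family history (1.0 to 1.5), and q the share of family-history-positive controls who have a first-degree ESKD relative (25% to 75%). Suppose positive family history is perfectly balanced, the true donation HR is 1, and the remaining 1,760 donors (unrelated, spouse, unknown) and their controls have risk 1. ESKD is rare, so the risk ratio approximates the HR:

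apparent HR = (4,854·R1 + 443·R2 + 1,760) / (5,297·[q·R1 + (1−q)·R2] + 1,760)

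| R1 | R2 | q | Calculation | Apparent HR |
|---|---|---|---|---|
| 2 | 1.5 | 0.75 | 12,132.5 / 11,691.9 | 1.04 |
| 3 | 1.0 | 0.50 | 16,765 / 12,354 | 1.36 |
| 5 | 1.0 | 0.25 | 26,473 / 12,354 | 2.14 |

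If every positive control had a first-degree ESKD relative (q = 1), the bias disappears or slightly reverses; with R1 = 3 and R2 = 1 it is 16,765/17,651 = 0.95. With no control of family history, and an assumed 10% of controls having such a relative (R2 = 1), the ratio would be 1.5 to 2.7 for R1 from 2 to 5. Balancing the single factor therefore helps, but may not be enough.

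**3. Reproducing the plan's power figures.** Inputs: "the type-1 error probability is set to 5" per cent (two-sided reproduces the figures), 80% power, and "we will be able to identify 3 controls for 98% of LDs". Schoenfeld formula: HR = exp(2.802 / √[D·a(1−a)]), with D = 0.98 × donors × (1 + k) × event proportion and a = 1/(1 + k).
- eGFR <45, 4,022 UMN donors, 3:1: D = 1,261 at 8% and 2,207 at 14%, giving 1.20 and 1.15. At 1:1 it gives 1.25 and 1.18. These match the article.
- Mortality at 11%, 7,057 donors: 1.124 (3:1) and 1.155 (1:1). The article says "we estimate that our minimal detectible hazard ratio with 80% power will be 1.13 for a 3:1 matching and 1.16 for a 1:1 matching", about 0.01 higher and conservative. The donor-weighted proportion, (0.12 × 4,022 + 0.07 × 3,035)/7,057 = 9.85%, gives 1.13 and 1.16.

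**4. The same formula in unrelated or spouse donors.**
- Mortality at 11%, 0.98 × 1,749 = 1,714 donors: D = 754 at 3:1, HR 1.27; at 1:1, 1.33. At 7%, the Mayo proportion, the 3:1 figure is 1.34.
- eGFR <45, 0.98 × 760 = 745 UMN donors, 3:1: D = 238 to 417, HR 1.52 to 1.37; at 1:1, 1.67 to 1.47.
- ESKD, for which the article gives no rate: at an assumed 0.2%, 0.5% and 1.0%, the 3:1 figures are 5.7, 3.0 and 2.2, against 2.4, 1.7 and 1.5 in all donors.

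**The case against.** The strongest reply is that the article never says family history is coded yes/no. Near fine balance can handle several levels, abstraction names CKD and ESKD separately, and the survey asks about family history of ESKD. The survey form and abstraction guidelines are not shown, and a condensed article may leave coding to them. This stands: a reader might infer binary coding from the description as a factor, from adjustment for its presence and from the search for any mention, but that is an inference. The supportable statement is that no grading is given.

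Three further stronger readings also fail.
- *The inherited risk stays in the donor effect.* Matching or adjustment removes part of it. What may remain is a residual of unknown size.
- *Unrelated donors are free of inherited risk.* They lack only the risk shared with the recipient. They may have a family history of their own, which Table 2 shows is collected. Matching them all to family-history-negative controls would bias the comparison in the direction one wants to avoid.
- *Unrelated donors go unused.* They are in every pooled analysis; what is absent is a separate one.

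Sensitivity group i closely resembles the primary control definition without family history, so setting the two side by side shows how far controlling the factor moves the estimate. It cannot show what remains within the factor. The modifier paragraph opens in general terms and the Discussion gives its modifiers as examples, so relationship is not ruled out. Still, the article does list its matching variables, sensitivity groups and modifiers, and none uses the relationship data for the confounder it singles out.

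**Conclusion.** The concern holds as a risk of residual confounding. It is not a demonstrated bias. On the article's own evidence, ESKD risk varies with kinship and more than two thirds of donors are first-degree relatives. As written, the matching could balance the recorded factor and leave part of the inherited risk in the donation effect, and no listed analysis would reveal it.

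The range of about 1.04 to 2.14 concerns ESKD and rests wholly on the assumed ratios and control mix; it illustrates what is possible and should not be quoted as an estimate. Firm figures are the Table 1 counts and, given the article's yield and event proportions, the detectable hazard ratios for mortality and eGFR <45. The change should be made, because it affects what the study can conclude about attributable ESKD risk.

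**What to change.** 1. Add donor-recipient relationship (first-degree, other relative, unrelated or spouse) to the named effect modifiers and report the donation effect by stratum. A control has no recipient, so each stratum of donors needs its own matched controls. A larger effect in first-degree donors would be compatible with residual confounding or with true modification, and the report should say so.
2. Add a sensitivity analysis restricted to the 1,749 Not Related and Spouse donors, matched on the donors' own recorded family history, for mortality, ESKD and (UMN only) eGFR <45. Report it beside the primary result.
3. Where chart or survey data allow, record whether a control's affected relative is first-degree and had ESKD, and balance on that level.

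The cost is plan wording and further matched analyses on data already held; item 3 may need some extra abstraction. The downside is precision. At 98% yield and 3:1 matching, the subset detects about 1.27 for mortality (11% events) and 1.37 to 1.52 for eGFR <45. Mayo supplies 989 of the 1,749 (57%), and 54.3% + 13.2% = 67.5% of Mayo donors donated from 2000 onward, so deaths may fall short of 11%. The ESKD result should be labelled supportive in advance.

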#### Control groups for sensitivity analysis

In addition to the set of controls selected for the primary analysis, we will consider additional broader groups from the REP from which to match. As in the primary control group, we plan to use sparse optimal 1:k matching to match REP patients in these groups to LDs.

i)REP patients for whom we can ascertain BMI, systolic and diastolic blood pressure, diagnosis of hypertension, smoking history, and normal renal function (normal serum creatinine, normal blood urea nitrogen, or normal urine protein). This group does not consider family history of CKD.ii)REP patients for whom we can ascertain BMI, systolic and diastolic blood pressure, diagnosis of hypertension, and smoking history with no known abnormal renal function (abnormal serum creatinine, abnormal blood urea nitrogen, or abnormal urine protein). This group does not consider family history of CKD or require renal function testing to have been done.iii)A group that does not consider family history of CKD, require renal function testing to have been done, or consider clinical characteristics (however, patients with known contraindications to donation would have already been excluded and those with known abnormal renal function will still be excluded).iv)Additionally, we will construct control groups using matching algorithms as close as possible to those used in previous studies[55, 56] to assess the effect of different matching criteria on the rates of each outcome.

For each control group (primary and sensitivity cohorts) we match to LDs, we will estimate the incidence rate of each outcome.

#### Statistical analyses details

Log-rank tests and Kaplan Meier curves will be used as preliminary assessments to compare the risk of all-cause mortality and cardiovascular mortality, CVD, ESKD, CKD (eGFR < 45; eGFR < 30 ml/min/1.73m^2^), proteinuria, DM, and hypertension after index date between LDs and healthy controls. Our study is powered based on these analyses. Cox proportional hazards models will also be used to test for an increased risk of adverse outcomes in living LDs versus controls while directly accounting for the variables used for matching (to account for any possible residual imbalance between the cohorts similar to how one may adjust for characteristics in a randomized controlled trial to account for residual imbalance and to improve efficiency). In analyses involving Mayo LDs and their associated controls we will account for donation center (Mayo vs. UMN) as a covariate in the model. If the proportional hazards assumption fails, an alternative method such as an accelerated failure time model will be considered. Indeed, the risk of mortality and ESKD may disproportionately increase with long-term follow-up on the 60-year scale of this study [123, 130, 131]. A similar approach will be used to test for increased risk of outcomes for LDs versus controls after development of DM, hypertension, proteinuria, de novo kidney disease, or pregnancies with gestational hypertension or preeclampsia, but additional measures (e.g. matching, adjustment) will be used to account for the time of disease onset.

In order to evaluate biases in the selection of controls and ascertain outcomes, we will compare the risk of non-kidney-related cancer between donors and controls using the previously described methods. As cancer risk is lower in donors than the general population, we expect a similar lower risk in controls [150]. If controls are well matched, we do not expect the risk of non-kidney related cancer to differ between donors and controls. If a difference in cancer risk is identified, it may indicate imbalance in our matching and it will be further investigated using methods described in Shi et al. [151].

We will also evaluate if the effect of donation differs across baseline characteristics (i.e. evaluate if a characteristic modifies the effect of donation) by testing the significance of the interaction term between donation and the characteristic in the model. These models will also allow us to assess the attributable risk of donation in LDs with certain characteristics at donation. We will specifically assess if age, BMI, smoking, donation eGFR, and race/ethnicity modify the effect of donation on ESKD and mortality. As a sensitivity analysis, the analyses will be repeated using a subset of REP controls having at least 5 years of medical history preceding the index date.

Logistic regression models fit using generalized estimating equations will be used to test for differences in the odds of gestational hypertension and preeclampsia between LDs and controls for all pregnancies occurring after the index date, while accounting for women having potentially multiple pregnancies. Adjustment variables to be considered in the model include: race/ethnicity, age at pregnancy, gravidity, and previous occurrence of pregnancy complications. Secondary analyses using logistic regression models will test for differences in the odds of these complications in the first pregnancy after the index date, adjusting for having previous pregnancies, and second pregnancy after the index date, adjusting for the occurrence of pregnancy complications in the first post-index date pregnancy.

A linear mixed effects model will be used to test the difference in the trajectory of eGFR over time between living LDs and healthy controls. This model will initially have a linear effect for time with subject-specific random intercepts and slopes, but natural splines will be used to investigate nonlinear temporal trajectories.

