A major innovative aspect of our study is our contemporaneous healthy matched control cohort. Unlike prior studies, we will more clearly delineate matched controls that reflect the health status of donors just prior to the date of donation. This will be accomplished by identifying controls known to be healthy and with normal renal function at the index date (matched to donation date) who are from the same geographical region of residence (Upper Midwest) as donors, and by obtaining granular data on controls to allow for optimal matching of controls to LDs on key characteristics (including family history of CKD).

Longitudinal follow-up of both LDs and REP controls provides detailed, uniquely available health information on events preceding ESKD and mortality. In contrast to previous studies, we will compare LDs and healthy-matched REP controls on the much more common intermediate endpoints (e.g., low GFR; CVD) that occur before ESKD or death. Additionally, we will be able to study outcomes of LDs who develop new comorbidities late after donation (e.g., obesity, hypertension, DM, early or late GFR < 45 ml/min/1.73m^2^, proteinuria). This will provide information about whether the impact of these comorbidities differs for those with 1 vs. 2 kidneys. That is, we will be able to assess if differences in long-term outcomes between donors and controls are mediated by differences in postdonation comorbidities.

We will be among the first studies to evaluate modifiers of the effect of donation on ESKD and mortality. There have been several studies of risk factors for developing ESKD in the donor population. However, these identified risk factors are also risk factors for ESKD in the general population. By using well-matched REP controls, we will be able to assess the effect of donation for “ideal” LDs and for LDs who, at donation, have risk factors for CKD. That is, ours will be among the first studies to test if the attributable risk of an outcome with kidney donation is modified by clinical and demographic factors (e.g., age, BMI, smoking, donation eGFR).

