### Dissemination

Findings from this study will be disseminated through peer-reviewed journals, conference presentations, and targeted dissemination/presentation to advocacy and stakeholder groups. To translate our findings into an understandable format for LDs and their care team we will develop a user-friendly long-term risk calculator. This freely available, interactive online calculator or app will allow candidate donors (and their providers) to estimate their risk of each outcome (including intermediate outcomes) at different time intervals with versus without kidney donation.

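### Kaplan-Meier curves for non-fatal outcomes and cardiovascular death overstate long-term absolute risk, and a Cox interaction term does not test whether the attributable risk is modified

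*Protocol article*

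**What the plan says.** Under Statistical analyses details the protocol article states: "Log-rank tests and Kaplan Meier curves will be used as preliminary assessments to compare the risk of all-cause mortality and cardiovascular mortality, CVD, ESKD". The list continues with CKD at two eGFR thresholds, proteinuria, diabetes and hypertension. Adjusted Cox models follow, with an accelerated failure time model as a fallback. The article does not say how death is handled for the outcomes other than all-cause mortality.

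The same section assesses effect modification by "testing the significance of the interaction term between donation and the characteristic in the model", naming age, BMI, smoking, donation eGFR and race/ethnicity as modifiers for ESKD and mortality. It adds that these models will serve to assess attributable risk in donors with given characteristics.

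The Discussion describes this as a study that will "test if the attributable risk of an outcome with kidney donation is modified by clinical and demographic factors". Under Dissemination, a calculator is to let candidate donors "estimate their risk of each outcome (including intermediate outcomes) at different time intervals with versus without kidney donation".

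One absolute measure is planned: under Control groups for sensitivity analysis, an incidence rate of each outcome for every matched control group.

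**The concern.** There are two separate mismatches between method and question.

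**Competing death.** Someone who dies can no longer develop ESKD, CKD or diabetes. A Kaplan-Meier curve for such an outcome can only count the death as censoring, so 1 − KM describes risk in a world without death. The actual cumulative incidence is lower, and the gap widens as deaths accumulate. Follow-up runs to as much as 60 years, mean age at donation is 39.02 years in the University of Minnesota cohort, and the plan itself expects mortality to climb over that span.

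**Scale.** An interaction term in a Cox model asks whether the hazard ratio differs between strata. Attributable risk with versus without donation is a difference in risk. If the modifier changes baseline risk, as age or BMI can be expected to, an equal hazard ratio means unequal risk differences, and equal risk differences mean unequal hazard ratios. A non-significant interaction could then be read as the same donation risk for all candidates when the absolute excess differs several-fold.

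**Working it through.** **1. The plan's power figures.** Schoenfeld's formula, inverted, with two-sided α = 0.05 (sidedness is not stated) and 80% power: HR = exp[(1.960 + 0.842)/√(D·p·(1−p))], where D = 0.98 × donors × (1+k) × event proportion and p = 1/(1+k).

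For eGFR < 45 (4022 donors, event proportion 8% to 14%):
- 3:1 matching: D = 1261 gives 1.200 and D = 2207 gives 1.148. Stated: 1.20 and 1.15.
- 1:1 matching: D = 631 gives 1.250 and D = 1104 gives 1.184. Stated: 1.25 and 1.18.

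For all-cause mortality (4022 + 3035 = 7057 donors, 11% dead) the formula gives 1.124 and 1.154 against the stated 1.13 and 1.16, so the plan is slightly conservative. These figures concern hazards. Log-rank and Cox with deaths censored target the cause-specific hazard, so none of them changes.

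**2. Size of the Kaplan-Meier excess.** Inputs from the document: 12% of University of Minnesota donors dead (Power), and index decades 99, 658, 796, 1040, 1200 and 229 (Table 1). Assumptions, not in the document: death hazard a·exp(0.09t), index dates spread evenly within decades, follow-up to 2022, and a rare outcome with hazard proportional to exp(gt), where g = 0, 0.05 or 0.08 per year.

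Survival is S(t) = exp[−(a/0.09)(exp(0.09t) − 1)]. Solving for 12% dead over all decades gives a = 0.00052, which implies 8%, 19% and 40% dead at 30, 40 and 50 years. For a rare outcome, (1 − KM)/(cumulative incidence) = ∫exp(gs)ds / ∫exp(gs)S(s)ds, both integrals from 0 to t.

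| g | 30 years | 40 years | 50 years |
|---|---|---|---|
| 0 | 1.024 | 1.051 | 1.106 |
| 0.05 | 1.034 | 1.083 | 1.204 |
| 0.08 | 1.039 | 1.101 | 1.262 |

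The excess is thus about 2-4%, 5-10% and 11-26%. If 20% were dead (assumed, to allow for uncounted deaths), it would be 20-53% at 50 years.

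A second model let mortality depend on age at donation, with the death hazard doubling every 8 years, and fixed eGFR < 45 at the stated 13.5%. It gives about 4%, 8-9% and 15-17% at the same horizons (for example 41.9% against 35.8% at 50 years).

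**3. Scale of effect modification.** With a constant hazard ratio of 1.5 and baseline risk p₀, the excess risk is 1 − (1 − p₀)^1.5 − p₀:
- p₀ = 0.1% (assumed): 0.05 percentage points.
- p₀ = 0.8% (assumed): 0.40 percentage points.

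That is an eightfold difference in attributable risk with a true interaction of zero on the hazard-ratio scale.

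**The case against.** Much can be said for the plan. Kaplan-Meier is called preliminary and is correct for all-cause mortality, the first outcome listed. Log-rank and cause-specific Cox compare hazards validly. Incidence rates are an absolute measure. A Cox model combined with baseline hazards and the hazard of death can yield subgroup risks even when the interaction is null. An article may leave the calculator's method to a fuller plan. All of this stands, and it limits the point. What remains is that the curves named would misstate absolute risk, that a single rate does not give risk by horizon when hazards rise, and that the step from Cox model to absolute risk is not described.

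It can also be argued that attributable risk could mean a fraction, for which a constant hazard ratio gives a roughly constant value. The with-versus-without wording under Dissemination points to a difference. If a fraction is meant, the article should say so.

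A reader might infer three stronger things that the document does not support:
- *That candidate donors will be shown 1 − KM.* No text assigns Kaplan-Meier to the calculator.
- *That the group comparisons or the power are wrong.* They are not (step 1).
- *That the excess reaches 35-105% at 50 years.* This follows from placing the 12% deaths at 22 years. But 22.04 years is the mean time to last survey or examination, while the 12% covers all index dates from 1963 to 2012. That hazard would imply 24% dead by 2018 and 30% by 2022 across the index decades.

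**Conclusion.** The point holds in limited form. For the non-fatal outcomes and cardiovascular mortality, the direction of the Kaplan-Meier error is certain; its size rests on the assumed hazards. It is small up to 30 years and matters at 40 to 50 years, the range the study's title advertises. Only the earliest donors reach 50 years: with follow-up to 2022 and an even spread within the 1970s, (99 + 45 + 0.2 × (658 + 271))/7057, or about 5%. The excess would be larger if the 12% undercounts deaths.

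The scale mismatch needs no mortality model. The test named under Statistical analyses details does not answer the question put in the Discussion, if attributable risk means a risk difference. The baseline risks in the example are illustrative.

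**What to change.** - For the non-fatal outcomes and cardiovascular mortality, present Aalen-Johansen cumulative incidence with death (for cardiovascular mortality, other death) as the competing event, in place of 1 − KM. Keep Kaplan-Meier for all-cause mortality.
- Keep log-rank and cause-specific Cox for hazard ratios.
- Define attributable risk as the standardised risk difference between donors and controls at fixed horizons, with confidence intervals, as far out as enough donors remain at risk.
- Report effect modification as the difference in risk differences between strata, beside the Cox interaction, and state that a null interaction does not show equal attributable risk.

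The cost is analysis wording and some code; no new data are needed and no power figure changes. The drawback is that additive contrasts for rare ESKD will have wide intervals.
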